**Study period**

Accrual, if the number of randomized participants reaches >300, then entry is stopped.

The trial ends when the last participant is followed up after the 2-year-old birthday.

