## **Follow-up**

Participating parent(s) are interviewed, and their children are examined from 1 to 24 months of age at the outpatient clinic of Jikei University Hospital. All infants undergo blood examinations to measure serum levels of total IgE and antigen-specific IgE at 5 and 24 months of age. Unscheduled visits and blood examinations are performed at the clinic when a participating infant has atopic symptoms, particularly when FA is suspected.

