## Study design

Randomized, controlled, parallel two-group trial at a single institution

Pregnant women during the third trimester are randomly assigned to either BF with or without amino acid-based EF, called the BF $\pm$ EF group, or BF plus CMF ( $\geq$ 5 ml/day from the first day of life to 1 month and  $\geq$ 40 ml/day after 1 month until weaning), called the BF+CMF group, in a 1:1 ratio. Infants are followed until they are at least 2 years of age. Follow-up is extended 1 year if participating infants have FA. When the mother needs to add more than 150 ml/day EF for 3 consecutive days to BF because of a low amount of breast milk, EF is switched to CMF. Thus, the offspring allocated to BF $\pm$ EF can avoid CMF for at least the first 3 days of life.

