## **Participants**

### **Inclusion criteria**

1. Be in a high-risk group for atopic sensitization: at least one of the father, mother, brothers, or sisters of infants has atopic diseases (asthma, atopic dermatitis, FA, allergic rhinitis, hay fever)

2. Obtained written informed consent.

a. Participants who understand randomization into two groups: BF with or without

amino acid milk and BF with CMF.

b. Blood examinations at 5-6 months and 2 years of age are required.

3. Be available to visit the outpatient clinic at 1 month, 2 months, 3 months, 4 months, 5 months, 7~8 months, 9~10 months, 12 months, 14~15 months, 18 months, and 24 months of age.

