#### **2. Asthmatic bronchitis**

A stringent index that includes frequent wheezing during the first 3 years of life and either one major risk factor (parental history of asthma or eczema) or two of three minor risk factors (eosinophilia, wheezing without colds, and allergic rhinitis).

Major Criteria

1. Parental asthma†

2. Eczema diagnosed by a medical doctor‡

3. Sensitization with elevated mite- or house dust-specific IgE  $\geq 0.10$  UA/ml

Minor Criteria

1. Allergic rhinitis diagnosed by a medical doctor§

2. Wheezing apart from colds

3. Eosinophilia ( $\geq 4\%$ )

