## **7. Blood sampling**

All infants undergo blood examinations to measure serum total and antigen-specific IgE.

- a. At the 5- to 6-month check-up prior to first solid food introduction:  
Egg white, cow's milk, wheat, mites.
- b. At 2 years of age:  
Egg white, cow's milk, wheat, mites, Japanese cedar pollen, dog dandruff, cat dandruff.
- c. Unscheduled visits are made to the clinic when participating infants have atopic symptoms, particularly suspicious of FA.  
e.g., exanthema just after eating an egg dish.

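### The exploratory asthmatic bronchitis index needs three years of wheeze history, but follow-up is planned to about 24 months, with a third year only for infants who have food allergy

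*Supplement*

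**What the plan says.** All references are to the final protocol and SAP in the Supplement.

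- **Outcome definition** (Exploratory outcomes, 2. Asthmatic bronchitis). The index requires "frequent wheezing during the first 3 years of life" plus either one major factor or two of three minor factors. The sentence names parental asthma or eczema as the major factor. The list beneath it has a third major criterion, "Sensitization with elevated mite- or house dust-specific IgE". Eosinophilia is one of the three minor criteria.
- **Length of follow-up** (Study design). "Infants are followed until they are at least 2 years of age. Follow-up is extended 1 year if participating infants have FA".
- **Visits** (synopsis, Follow-up; Participants, Inclusion criteria). According to the synopsis, "their children are examined from 1 to 24 months of age at the outpatient clinic". The visit list ends with "12 months, 14~15 months, 18 months, and 24 months of age".
- **End of trial** (synopsis, Study period). "The trial ends when the last participant is followed up after the 2-year-old birthday". The SAP's Study period section plans three years of accrual and two years of follow-up, five years in all.
- **Blood tests** (7. Blood sampling). Total IgE and antigen-specific IgE are measured. Mite IgE is in both the 5- to 6-month and the 2-year panels; the 2-year panel adds "Japanese cedar pollen, dog dandruff, cat dandruff". Eosinophil counts are not listed.
- **Status**. Immediate-type FA is secondary outcome I. Asthmatic bronchitis is exploratory and is to be reported on a separate occasion.

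**The concern.** The outcome window is a year longer than the observation planned for most infants. The only planned route to the missing year is a rule triggered by FA, a post-randomization event that the feeding strategy is meant to change. If year-3 wheeze enters the score, infants with FA have more time in which to become a case, and an arm with more FA would appear to have more asthma even if feeding had no effect on wheeze. Such a result would be easy to mistake for a real effect, because it runs in the same direction as the trial's main hypothesis. If year-3 wheeze does not enter the score, the outcome as worded is not observed in full for anyone.

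The same definition leaves two smaller matters open: whether mite sensitization is a major criterion, and where the eosinophil counts are to come from.

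**Working it through.** The plan gives no figure for this outcome, so there is nothing to reproduce. The check compares time windows and then sizes the consequence under stated assumptions.

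**1. Windows**

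| | Window needed | Planned observation | Share covered |
|---|---|---|---|
| Infant without FA | 3 years | 2 years | 2/3 = 67% |
| Infant with FA | 3 years | 2 + 1 = 3 years | 100% |

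The five-year plan (3 + 2) leaves no stated room for the extra year in late-enrolled infants with FA, so even that group may not all reach age 3 under observation.

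**2. Two readings**

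- *Extension-year wheeze counts.* Ascertainment is 67% or 100% of the window according to FA status.
- *Extension-year wheeze does not count.* Every infant has 2 of the 3 years, so nobody is scored on the window as defined.

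No section fixes a common age for judging the outcome, limits wheeze to 24 months, or gives an analysis that allows for unequal observation time.

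**3. Size under the first reading, with no true effect**

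Assumptions, none of them given in the documents:
- the wheeze hazard is constant and is the same with and without FA;
- every infant with FA completes year 3;
- q2, the 2-year risk of meeting the index, is 5% to 20%;
- f, the share of an arm with FA, takes the values shown in the table below.

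The 3-year risk is q3 = 1 − (1 − q2)^1.5.

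- q2 = 0.05: q3 = 0.0741, ratio q3/q2 = 1.48
- q2 = 0.10: q3 = 0.1462, ratio 1.46
- q2 = 0.20: q3 = 0.2845, ratio 1.42

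The observed risk in an arm is (1 − f)·q2 + f·q3. For q2 = 0.05:
- f = 0.05 gives 0.95 × 0.05 + 0.05 × 0.0741 = 0.0512
- f = 0.15 gives 0.85 × 0.05 + 0.15 × 0.0741 = 0.0536
- The risk ratio (RR) is 0.0536/0.0512 = 1.047

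| FA by arm | q2 = 0.05 | q2 = 0.10 | q2 = 0.20 |
|---|---|---|---|
| 5% v 5% | RR 1.00 | 1.00 | 1.00 |
| 5% v 15% | 1.047 | 1.045 | 1.041 |
| 10% v 25% | 1.069 | 1.066 | 1.061 |
| 5% v 30% | 1.117 | 1.113 | 1.103 |

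The risk difference is (f2 − f1)(q3 − q2).
- Smallest, at 5% v 15% and q2 = 0.05: 0.10 × 0.0241 = 0.0024, or 0.4 of an infant in an arm of 150.
- Largest, at 5% v 30% and q2 = 0.20: 0.25 × 0.0845 = 0.0211, or 3.2 infants in an arm of 150.

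**4. Criteria set against the blood panel**

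- An infant with frequent wheeze and mite sensitization as the only risk factor is positive by the list and negative by the sentence.
- Mite IgE is measured in all infants. Eosinophils are in neither scheduled panel, so that minor criterion could be met only where a count happened to be done.

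**The case against.** The strongest reply is that the unequal windows are inferred. A reader might take the plan to state that asthma is counted to age 3 in infants with FA and to age 2 in the rest. It does not. The extension is tied to FA alone, no asthma assessment is attached to it, and the second birthday is the closing point almost everywhere else. If asthma were judged at 24 months in everyone, the differential window would vanish. This stands as a limit on the bias claim, but it does not remove the mismatch: under that reading the 3-year window is unobserved in all infants.

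A reader might also infer a large false effect. A risk ratio of 1.32 can be produced with a 2-year risk of 5%, a year-3 onset risk of 20% and FA of 5% v 15%: 0.05 + 0.95 × 0.20 × 0.05 = 0.0595 against 0.05 + 0.95 × 0.20 × 0.15 = 0.0785. That makes onset in one year four times the risk of the first two years together, and nothing in the documents supports it.

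It can further be said that the SAP names no method for exploratory outcomes beyond a general intention-to-treat statement. That is true. The separate report would nevertheless rest on this definition.

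Lastly, a reader might conclude that the sensitization criterion cannot be assessed because house-dust IgE is not in the panel. That does not follow, since the criterion accepts mite or house dust and mite IgE is scheduled for every infant. Some criteria also carry footnote marks whose text is not shown, so the list as read may be incomplete.

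**Conclusion.** The concern holds in a limited form. The 3-year wheeze window does not fit a follow-up planned to about 24 months, and the only planned third year is conditional on a trial outcome. As worded, the outcome either is ascertained according to FA or cannot be scored as defined.

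The between-arm bias is conditional. It requires that extension-year wheeze is counted and that FA differs between arms. Under the constant-hazard illustration it is modest, with a risk ratio of about 1.04 to 1.12, and it is absent if FA is equal. The FA shares and wheeze risks are assumptions.

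The disagreement over mite sensitization and the unscheduled eosinophil count are real but small. The outcome is exploratory and separately reported, and the primary outcome, the FA-related secondary outcomes and the sample size are untouched. This is a minor-priority change.

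**What to change.** - Define the between-arm asthmatic bronchitis outcome on wheeze from birth to the 24-month visit for all infants. State that information from the FA extension year is excluded from that comparison, and label the outcome a 2-year modification of the cited index.
- Make the sentence and the list agree on whether mite sensitization is a major criterion.
- Use eosinophilia only if it is measured in all infants. Otherwise drop it and restate the minor-criteria rule explicitly, because two of three no longer applies when two criteria remain.

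**Cost.** If eosinophilia is dropped, the change is to wording only, with no new visit, blood test or sample-size consequence; keeping it means adding a count for every infant. The modified outcome will not be directly comparable with the 3-year index, and removing a minor criterion changes who qualifies, so both points should be stated in the report.

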#### **3. Sensitization to Japanese cedar pollen**

Japanese cedar pollen-specific IgE  $\geq 0.10$  UA/ml

#### **4. Allergic rhinitis**

Allergic rhinitis: Rhinitis signs and symptoms for 1 month and mite-specific IgE  $\geq 0.10$  UA/ml

#### **Safety outcomes**

The following are obtained from an interview at the outpatient clinic just after the 2-year-old birthday.

1. Admission for any reason
2. Emergency room visit for any reason
3. Growth retardation: Height and weight at 2-year-old birthday

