### III. Data monitoring

A) Randomization using a block of four by [name] who does not interview participating families and does not examine their infants.

B) Data monitoring

If the frequency of adverse events deviates in either intervention group, the committee reports the data to the Safety and Data Monitoring Committee as well as the lead investigator.

a. [name]., Ph.D. (physician and nephrologist)

b. [name] (secretary at Molecular Epidemiology)

Division of Molecular Epidemiology

The Jikei University School of Medicine

Tokyo, Japan

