#### **IV. Safety and Data Monitoring Committee**

a. Judging from data of interim analysis, this committee may recommend stopping or continuing the trial.

b. Responding to a report of adverse events, the committee may recommend stopping the trial or allowing the trial to continue.

① [name]., Ph.D.

② [name]., Ph.D.

③ [name]., Ph.D.

Department of Pediatrics

Sagamihara National Hospital

Kanagawa, Japan

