### 3. Study period

We assume that 100 pregnant women per year will participate in this trial. Therefore, the accrual period will be 3 years. The last infant is followed up 2 years later. Thus, a total of 5 years is predicted to be needed to accomplish this trial.

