### Safety

Many Japanese maternity wards recommend BF, but allow mothers or nurses to help by supplying CMF to supplement BF after feeding colostrum, e.g., 6 to 10 hours after birth.

This is a food intervention trial. Thus, basically no safety concerns exist. However, the following are compared.

- a. Admission due to any disease
- b. Emergency visit or admission for any reason
- c. Body height and weight at 24 months of age

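### Admissions and emergency visits are collected by one interview of unblinded parents after the second birthday, and the adverse-event route to the safety committee has no stated source or schedule

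*Supplement*

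**What the plan says.** All references are to the final protocol.

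- **Outcomes and source.** The Safety outcomes section lists admission for any reason, emergency room visit for any reason, and growth (height and weight at the second birthday). It introduces them with: "The following are obtained from an interview at the outpatient clinic just after the 2-year-old birthday". The Safety section repeats the list, giving "Emergency visit or admission for any reason" and "Body height and weight at 24 months of age", and adds no earlier time and no other source.
- **Analysis.** Planned methods of analysis, item d, compares safety outcomes by risk ratio, risk difference and 95% CI, or by Student's t test.
- **Oversight.** III. Data monitoring says: "If the frequency of adverse events deviates in either intervention group, the committee reports the data to the Safety and Data Monitoring Committee". IV. Safety and Data Monitoring Committee adds that, on such a report, "the committee may recommend stopping the trial or allowing the trial to continue". Neither section defines an adverse event, says who records it and at which visit, sets a tabulation interval, or says how large a deviation triggers a report.
- **Blinding.** Families are not blinded. The study pediatrician who sees them in the outpatient clinic up to 24 months is not blinded either (Blinding to allocation group; Flow of participants, item 3). The blinded endpoint committee rules on food allergy only.
- **Contacts.** Flow of participants, item 3, provides at least seven interviews with examination: at 1, 3, 5-6, 9-10, 12, 18 and 24 months. Further ages appear in brackets.

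**The concern.** The randomised feeding lies in the first five months or so of life, whereas the stated collection point for admissions and emergency visits is age two. Two consequences follow.

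1. **Measurement.** Parents are asked to look back over 24 months, and the part that matters most for the intervention is the most distant. Both the parents and the clinic pediatrician know the arm. The plan states no check against hospital records, and the blinded adjudication does not reach these events. Recall error of this kind can dilute a difference, or bias it if reporting differs by arm. A family lost at, say, 12 months contributes no information even on the feeding period.
2. **Oversight.** To detect that event frequency deviates between arms, someone must hold counts by arm while infants are being enrolled and fed. The only all-cause events with a stated collection rule arrive too late for most of that time, and the separate adverse-event route has no written input.

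**Working it through.** **Inputs from the plan**

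- Accrual (Study period): "We assume that 100 pregnant women per year will participate in this trial", for 3 years, so a = 100/12 = 8.33 women per month, N = 300, with the last woman randomised at month 36.
- Follow-up (same section): "The last infant is followed up 2 years later".
- Randomisation (Study design): "Pregnant women during the third trimester are randomly assigned".
- Feeding period: to 5 months of age or start of solid food in the BF+CMF arm (synopsis, Intervention).
- Interim analyses: when 100 and 200 infants have passed the second birthday.
- Assumed loss to follow-up: 3%.

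**Assumptions.** Accrual is uniform. The lag from randomisation to birth, L, is 0 to 3 months. The interview takes place at age 24 months.

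**The plan's own figure.** 300/100 = 3 years of accrual, plus 2 years of follow-up, gives the stated 5 years. With the lag it is 5.0 to 5.25 years.

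**Step 1: distance from the feeding period.** 24 − 5 = 19 months, so 19/24 = 79% of the recall window lies after feeding.

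**Step 2: first possible interview.** It falls at month 24 + L, that is, months 24 to 27.
- Women randomised by then: a × (24 + L) = 8.33 × 24 = 200 (67%) to 8.33 × 27 = 225 (75%).
- Infants already past 5 months: a × (24 + L − L − 5) = 8.33 × 19 = 158.

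**Step 3: end of accrual (month 36).** Interviews possible: a × (36 − 24 − L) = 100 for L = 0, and 75 for L = 3, which is 33% to 25% of 300.

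**Step 4: 100 infants past the second birthday.** The 100th woman is randomised at month 12, so her infant turns two at month 36 + L, that is, months 36 to 39 (about year 3.1 at the midpoint).
- Accrual is complete.
- Infants past 5 months: a × (36 + L − L − 5) = 8.33 × 31 = 258.
- Unborn or under 5 months: 300 − 258 = 42 (14%). L cancels, so this does not depend on the lag. If feeding is taken to run to 6 months, the figure is 8.33 × 6 = 50 (17%).

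**Step 5: 200 infants past the second birthday.** This falls at month 48 + L. The last infant reached 5 months at month 41 + L, so none remains in the feeding period.

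**Step 6: missing families.** At the plan's 3%, 0.03 × 300 = 9 children would have no admission or emergency-visit data for any age. The e-mail contact described under Efforts to reduce loss to follow-up concerns food allergy; the text does not extend it to these events.

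**The case against.** The strongest reply is that the safety *outcomes* and *adverse-event reporting* are separate matters. The first are compared at the end. The second is a route of its own, listed separately from the interim analysis, and nothing ties it to the 24-month interview or makes it wait for 100 second birthdays. Infants are also seen at 1, 3 and 5-6 months, ward intake is monitored daily, and unscheduled visits allow examination on the same or next day for allergic signs. This stands. A reader might infer that the committee has no data, or that harm during feeding could not be seen; the documents support neither. What they lack is a rule for turning these contacts into recorded, tabulated events. The unscheduled visits are also directed at atopic symptoms rather than all-cause admission.

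Three further points have weight:

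- Height and weight at 24 months are measurements at that visit, so the recall criticism covers two of the three outcomes, not the whole safety comparison.
- No case-report form is shown, so earlier recording may happen in practice. The written plan, however, names the later interview as the source, and that is what an analyst would follow.
- The documents give no event rate and no evidence on the direction or size of differential recall. Bias between the arms is a possibility, not a demonstrated effect.

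Finally, the Safety section treats formula supplementation as ordinary ward practice with basically no safety concerns. That lowers the urgency. It does not explain choosing the weaker of two available ways to collect outcomes the plan has decided to compare.

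**Conclusion.** The point holds for admissions and emergency visits. As written, their comparison rests on unblinded parental recall of up to two years, collected about 19 months after feeding ends, with no data from families lost earlier. None of these interviews can take place during a child's own feeding period, or before about 67% to 75% of women are randomised. When 100 infants have reached age two, accrual is over and about 42 of 300 infants (14%) are still unborn or under 5 months. These timings rest on uniform accrual at the planned rate and, for the 67% to 75%, on the assumed lag of 0 to 3 months.

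The adverse-event route to the committee is real but lacks a stated definition, source, schedule and threshold. The fault is therefore an unspecified input, not an absence of oversight. The primary outcome is a laboratory measurement, and neither it nor the sample size is affected. This should be fixed because a better method is available at little cost; it does not threaten the main result.

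**What to change.** - At each existing visit (1, 3, 5-6, 9-10, 12, 18 and 24 months), record every admission and emergency visit since the last visit, with date and reason, and record weight and length.
- Name these visit records, rather than the 24-month recall, as the source for the safety risk ratios and risk differences. Families lost later then still contribute their earlier months.
- In III. Data monitoring, state what counts as an adverse event and where it is recorded, and send tabulations by arm to the Safety and Data Monitoring Committee at fixed calendar intervals during accrual.

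The cost is a few added form lines and periodic tabulation work. No new visit or procedure is needed, and the sample size does not change. The parents and the clinic pediatrician remain unblinded, so the change shortens the recall period but does not remove that source of bias.

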### **Flow of participants**

#### **1. Informed consent and registration**

- a. Pregnant women and their husbands are informed about the trial in detail at a childbirth class during late pregnancy through a talk by [name] and the informed consent document. Written, informed consent is sent to the data monitoring center at the Molecular Epidemiology Division of Jikei University School of Medicine.
- b. Current or previous family history of atopic diseases (asthma, atopic dermatitis, FA, allergic rhinitis, hay fever) is obtained through questionnaires as well as parental demographic information such as maternal age and body weight/height. Only pregnant women who are confirmed to have a family history of atopic diseases are included.
- c. Food questionnaires of mothers (Appendix 3) are taken during the third trimester of pregnancy and at 1, 3, and 5 months of age after birth.

